## Abstract

**Background::**

Peritoneal metastases from gastrointestinal or gynecologic malignancy are a prominent part of the natural history of these diseases. Peritoneal metastases, if not effectively treated, will result in a decreased survival and cause an impaired quality of life. Hyperthermic intraperitoneal chemotherapy (HIPEC) is a treatment specifically designed to combat peritoneal metastases. A group of patients who, from a theoretical perspective, may benefit from HIPEC are those patients with a positive peritoneal cytology. In order to identify these patients at the time of a surgical intervention, a same day cytology is to be performed.

**Materials and methods::**

The result of this test is to be available at or before the completion of the cancer resection. If the cytology is positive, the patient immediately becomes a candidate for HIPEC. The HIPEC will be of maximal value if a complete cytoreduction, as judged by the surgeon, has been possible. This phase 1 trial is to demonstrate that the Surgical Oncology Service, the Department of Pathology, the Pharmacy and the Operating Room personnel can co-ordinate a phase 1 protocol to successfully complete the same day cytology with an efficient delivery of HIPEC. A standardized plan for consent, cytology collection, preparation of the specimen, reading of the specimen, reporting the results in a timely manner facilitates the administration of HIPEC in peritoneal cytology positive patients.

**Dissemination::**

Successful completion of these requirements is a positive result for this study and allows for future protocols to be generated. Successful completion of the same day cytology phase 1 protocol will allow the efficacy, safety, and efficiency of this plan of patient management to be evaluated.

HighlightsThe determination of positive versus negative peritoneal cytology at the time of a surgical intervention is not currently routinely performed.The methodology for making the results of peritoneal cytology available in the operating theater is not currently in use.A standardized use of hyperthermic intraperitoneal chemotherapy (HIPEC) is in patients with positive peritoneal cytology.A workable protocol to identify positive peritoneal cytology during a surgical procedure as an indication for HIPEC is a necessary first step toward improved patient care.Optimal management plans for patients found to have positive peritoneal cytology at the time of a surgical procedure need to be determined.

## Background and rationale

### Credits and debits regarding the use of HIPEC

Peritoneal metastases are a prominent part of the natural history of many abdominal and pelvic malignancies. Elimination of this site for metastatic disease may improve survival and, if not, improve survival have a positive impact on quality of life. Quality of life improvements would come about by prolongation of gastrointestinal function.

From a pharmacologic perspective, administration of cancer chemotherapy directly into the peritoneal cavity results in a regional dose intensity that can be exploited for greater cytotoxicity^1^. Hyperthermia within the peritoneal cavity to 42°C can augment this dose intensity. These positive aspects of intraperitoneal chemotherapy are diminished by the limited penetration of drugs of only a few cell layers into cancer nodules or the peritoneal surface contaminated by cancer cells. This limited penetration occurs because it is driven by simple diffusion. A high concentration of cancer chemotherapy within the chemotherapy solution causes a movement of drug into the low concentration within tumor nodules. If the tumor nodule is vascularized, the cancer chemotherapy will be rapidly moved into the body compartment. If the high concentration of chemotherapy is removed from the peritoneal space, it may be rapidly eluted from the cancer nodule.

### Delay in the administration of HIPEC as a cause of treatment failure

If cancer cells are placed into the peritoneal cavity of an experimental animal, intraperitoneal chemotherapy can be used effectively to control the progression of peritoneal metastases. However, this regional chemotherapy treatment is not effective if the intraperitoneal administration of chemotherapy is delayed. Simultaneous inoculation of the cancer cell suspension and cancer chemotherapy is the most effective. After a 1 h delay, effects of treatment are reduced. After 24 h, the benefits of intraperitoneal chemotherapy are gone^2^.

In current practice, peritoneal cytology is often sent at the beginning and sometimes at the end of a cancer resection. The results are available within 3–4 days because the cell block is not available until this time. These delayed results provide valuable information regarding staging and prognosis. However, they are of no therapeutic benefit. The free intraperitoneal cancer cells have become tightly adherent to resection sites and traumatized peritoneal surfaces. They are trapped within a matrix of organized fibrin and are no longer accessible to intraperitoneal chemotherapy.

In contrast, same day cytology would give the oncologic surgeon information that could be used therapeutically. It would allow HIPEC to be used as part of a cancer resection. The patients most likely to benefit from HIPEC would be identified and available for treatment with optimal timing. An efficient and cost-effective execution of same day cytology is the goal of this protocol.

### Treatment of cancer cells loosely adherent to surfaces of the abdomen and pelvis

These debits of intraperitoneal chemotherapy delivery are avoided and credits maintained if the target for the intraperitoneal chemotherapy is single cancer cells within the peritoneal fluid. This type of cancer spread is identified by a positive peritoneal cytology. A second target that can be treated by intraperitoneal chemotherapy is cancer cells disrupted as a result of surgical trauma that have become loosely adherent to parietal or visceral peritoneal surfaces^3^. These cancer cells accumulate on raw tissue surfaces, especially at the sites of cancer resection. They are single cells that can be dislodged from the traumatized tissue surfaces by large volumes of intraperitoneal chemotherapy solution. To eradicate free intraperitoneal cancer cells and cancer cells loosely adherent to abdominal and pelvic surfaces, the warm chemotherapy solution must flood the peritoneal cavity with a relative uniform distribution. For best results, this peritoneal lavage must occur soon after the complete resection of the primary cancer and the complete resection of any tumor nodules that are securely attached to peritoneal surfaces. Delay in the delivery of the intraperitoneal chemotherapy solution will allow the cancer cells to be trapped within an organized fibrinous layer that will occur within a few hours as part of the healing process.

### Increasing the viable targets for HIPEC with same day cytology

The minimal or absent HIPEC effects demonstrated to date result from HIPEC application in clinical situations in which HIPEC has little or no efficacy^4^. A plan to use HIPEC only when the heated chemotherapy solution has free cancer cells as a target is possible with the initiation of a program in ‘Same Day Cytology’. This clinical tool would provide information to the surgical oncologist regarding the presence of free intraperitoneal tumor cells. These cells identified by positive cytology are the most efficient target of HIPEC. If the same day cytology report returns positive, an appropriate HIPEC for a particular disease should be administered. There may be some clinical situations in which HIPEC may be indicated even if the same day cytology is negative. For example, if a very extensive resection of an advanced gastric cancer is required, the likelihood of cancer cells released as a result of surgical trauma is large. Information regarding peritoneal cytology as positive after gastrectomy is not likely to be available to the surgeon in a timely manner to decide if HIPEC is indicated. In some clinical situations, the HIPEC should be administered in the absence of information regarding positive cytology.

### Low-grade appendiceal mucinous neoplasm with peritoneal metastases – possible benefits of HIPEC

The low-grade appendiceal mucinous neoplasms cause extensive accumulation of mucus and numerous strips of minimally atypical epithelial cells. These cells are not invasive into the peritoneum so they are easily dislodged from a surface to which they are adherent. The HIPEC can destroy the large number of cells that remain after cytoreduction within the free peritoneal space and loosely adherent to structures within the abdomen and pelvis. The mucus that surrounds each cell may act as a reservoir for chemotherapy solution and thereby increase the residence time of the chemotherapy. Cytoreductive surgery plus HIPEC is accepted as a standard of care for low-grade appendiceal mucinous neoplasms^5^.

### Colorectal cancer peritoneal metastases – possible benefits from HIPEC

A positive impact on the occurrence of local-regional disease has been demonstrated in T4 colon cancer^6^. As expected, HIPEC mitomycin C was effective in controlling free cancer cells present within the peritoneal spaces if gross disease was not present at other sites. In contrast, HIPEC is expected to be less effective in treating established peritoneal metastases. In patients with peritoneal metastases from colon cancer only 50% of patients will have a positive cytology^7^. Many patients, in the absence of free cancer cells, will not have a target for HIPEC. A single cycle of HIPEC for metachronous peritoneal metastases can only be expected to result in benefit for a small proportion of patients.

### Gastric cancer peritoneal metastases – possible benefits from HIPEC

Gastric cancer with peritoneal metastases has a high incidence of peritoneal metastases and positive peritoneal cytology. The chemotherapy agents used for gastric cancer HIPEC are usually effective and the destruction of free cancer cells or cells loosely adherent to peritoneal surfaces is expected. Control of free cancer cells and their elimination from the resection site and other abdominal and pelvic surfaces will result in an absence of peritoneal metastases that would progress in the future^8^. Larger nodules, vascularized nodules or cancer cells caught up in scar will not be eliminated.

### Ovarian cancer – possible benefits from HIPEC

Ovarian cancer with peritoneal seeding has clinical features that are likely to be benefitted by HIPEC. First, in a large majority of patients free intraperitoneal cancer cells are present as positive cytology. In addition, after the cytoreductive surgery to resect the ovarian cancer the abdominal and pelvic surfaces are contaminated by cancer cells spread around the peritoneal cavity as a result of the trauma of surgery. These loosely adherent cells are targets for an effective HIPEC. As a result of this eradication of cancer cells by HIPEC at the time of surgery, scar tissue infiltrated by tumor can be avoided. The layer of cancer-contaminated scar can be prevented by HIPEC. Tumor cells trapped in scar tissue are an ineffective target for HIPEC. Also, tumor cells trapped in scar are not an effective target for systemic chemotherapy. Elimination of tumor cell entrapment in scar would cause HIPEC to improve the outcome of patients with ovarian cancer. The systemic chemotherapy with cisplatin and paclitaxel is expected to be effective at systemic sites but minimally effective for poorly vascularized tumor trapped within scar tissue^9^.

### Endometrial cancer peritoneal cytology – possible benefits from HIPEC

The predominant anatomic sites for endometrial cancer dissemination are not the peritoneal surfaces. Only ~10% of patients with disease confined to the uterus have a positive peritoneal cytology. These patients have a reduced prognosis and the recurrence of disease is, in a majority of cytology positive patients, as peritoneal metastases^10^. Same day cytology would identify these patients and reduce, probably eliminate, progression of peritoneal metastases in this special group of patients. Any improvement in long-term survival would need to be established with a randomized trial.

### Incidence of free cancer cells in the absence of gross peritoneal metastases in gastrointestinal and gynecologic cancers

Rekhraj and colleagues performed a meta-analysis to determine the impact of free intraperitoneal cancer cells on survival of primary colon cancer resections. They reported on nine studies with a total of 1182 patients. Free cancer cells were detected prior to resection in 125/822 (15.2%) of patients and in 64/533 (12%) of patients following resection. Positive peritoneal cytology was associated with a significantly higher incidence of overall recurrence in both preresection and postresection groups^11^.

In patients with gastric cancer, a preoperative and postoperative peritoneal cytology has become a standard of care and is an important independent prognostic indicator. Positive peritoneal cytology moves a patient into the stage pM1 pathologic classification according to the Eighth Edition of the American Joint Cancer Staging Manual^12^. At Memorial Sloan-Kettering Cancer Center, 1241 patients had laparoscopy preoperatively as staging for gastric cancer. They report 93 patients (32%) without gross evidence of advanced disease (no peritoneal metastases detected) with positive peritoneal cytology. They conclude that patients with positive peritoneal cytology as the only evidence of advanced disease exhibiting a poor outcome^13^.

For ovarian cancer, the incidence of visible peritoneal metastases approaches 100%. Peritoneal cytology is used to confirm the diagnosis but would not be the indication for a HIPEC procedure. Peritoneal cytology is suggested to be of value in women with uterine leiomyosarcoma. Matsuo and coworkers reported on 1481 uterine sarcomas. Malignant peritoneal cytology was present in 146 patients (9.9%)^14^. Also, positive peritoneal cytology was reported as an independent risk factor in patients with early stage endometrial cancer^15^.

In summary, peritoneal cytology is often positive in the absence of visible peritoneal metastases or other evidence of disseminated disease. The present of peritoneal metastases has a profound impact on prognosis. Survival may be improved if HIPEC is used in a timely manner on this subset of patients.

### Summary regarding the use of HIPEC

The use of HIPEC in gastrointestinal and gynecologic malignancy has been used in many clinical situations that were unlikely to result in benefit. Only single cells suspended within the chemotherapy solution are reliably destroyed by a single HIPEC treatment. Visible nodules even less than 1 mm, vascularized nodules or plaques, and tumor cells layered out in scar tissue are not an effective target for HIPEC. Destruction of free intraperitoneal tumor cells and prevention of cancer from being entrapped in scar tissue can eliminate a major site for systemic chemotherapy failure. In order to confirm that patients with a high likelihood of benefit from HIPEC do exist, the routine application of same day cytology is recommended.

### Goals of this protocol

The aim of our study is to show that HIPEC can be used as a planned part of a resection of an abdominal or pelvic malignancy in order to eradicate free intraperitoneal cancer cells and cancer cells loosely adherent to traumatized abdominal or pelvic surfaces. To this point in time, identification of the patients who will benefit from HIPEC has not been definitively established. The hypothesis of our study is that a positive peritoneal cytology identifies a patient who, along with a complete resection of visible disease, will benefit from HIPEC. In the current phase 1 study, the results of the peritoneal cytology can be made available with 3–4 h. A positive result causes the patient to be a candidate for HIPEC. Positive results of the same day cytology are used as an indication for HIPEC if the cancer resection is complete.

## Methods/design

### Objectives

The goal of this study is to demonstrate the feasibility of a same day cytology to select patients with a complete cancer resection for HIPEC. In order for this strategy to be successful the Surgical Oncology Service, the Department of Pathology/Cytology, the Hospital Pharmacy, and the Operating Room personnel must provide a coordinated effort.

### Methods

A first requirement is preoperative consent for HIPEC in gastrointestinal and gynecologic malignancy patients having abdominal-pelvic surgery for cancer (Tables 1, 2). Patients with a primary or recurrent cancer will require not only a standard consent for complete resection of the malignancy but also consent for HIPEC.The surgical procedure scheduled with the operating room must also include collection of the same day cytology specimen and possible administration of HIPEC. In order to avoid unnecessary delay, the equipment required for same day cytology must be available prior to the start of the surgical procedure. Also, the administration of the standard HIPEC for gastrointestinal or gynecologic malignancy must be possible with a few minutes notice.Collection of the same day cytology specimens: The same day cytology specimen is to be collected just after access to the abdomen and pelvis has been obtained (Fig. 1). Adhesions should be lysed to gain visual access to the right upper quadrant, right paracolic sulcus, left paracolic sulcus, and deep pelvis. An exploration of the abdomen and pelvis with a full description of the findings should be recorded in the operative note dictated by the surgeon. Prior to collection of the same day cytology specimen lysis of adhesions or surgical dissection that results in bleeding must be avoided. A bloody same day cytology specimen is more difficult to read. Also, blood contaminates the peritoneal fluid and will dilute the number of malignant cells identified.Four specimens of 50 ml each are to be obtained from each patient. If the patient has ascites no saline irrigation is required. Forcibly instill 50 ml into the right upper quadrant (superior and inferior to the liver), into the right paracolic sulcus, into the left paracolic sulcus, and into the deep pelvis posterior to the rectum. If the peritoneal fluid collection from each anatomic site is not equal to 50 ml, instill the volume of saline needed to provide a 50 ml specimen. The aspirations each containing 50 ml, should be contained in a suction container dedicated to the recovery of 200 ml of peritoneal fluid aspirate. It should leave the operating room table and be handed off to go to the cytology laboratory (800 cc Suction Canister, Cardinal Health Inc.).One of the assumptions of this phase 1 study is that a lavage of four anatomic sites at the time of the exploration of the abdomen and pelvis in a surgical procedure produces a higher likelihood of a positive result that a paracentesis. If same day cytology is available, it can simplify patient management and reduce the incidence of false negative peritoneal cytology.Preparation of the same day cytology specimen for the pathologist/cytologist: The 200 ml suction container is handed off the operating table, immediately uncapped and 500 units of heparin added. The 200 ml suction container is swirled to disperse the heparin. The 200 ml of peritoneal irrigation fluid or ascites are transferred to the Pathology/Cytology Department. Tubes containing the peritoneal fluid are centrifuged at 2000 rpm for 10 min. The fluid is suctioned off taking care to preserve the cellular pellet at the base of each tube. The cellular pellets from three tubes are agitated by pipette and transferred to the fourth tube. This tube is recapped, centrifuged, and transferred to the pathologist/cytologist for staining and reading.Staining and reading of the same day cytology specimen: A portion of the sediment is smeared on four glass slides. Two slides should be smeared with ~1 ml of sediment and prepared for microscope study by the Papanicolaou thin prep method. Two slides should be smeared with ~1 ml of sediment and allowed to air dry. They will be prepared for microscope study by the Diff Quick method. The remainder of the cellular pellet is submitted for cell block. Hematoxylin and eosin stain and appropriate immunostains for the malignancy being treated will supplement the same day cytology report several days later.Interpretation of the slides for same day cytology: A slide should be interpreted as positive if clusters of or individual cells are detected. For an experienced cytopathologist differences between cancer cells and reactive mesothelial cells should be apparent.Time allowed for the final report for the same day cytology: The primary goal of this pilot study is to demonstrate the feasibility and reproducibility of the same day cytology. To be successful the results of the cytology must be available when the cancer specimen is removed. A 3 h time allowed for the final report of the same day cytology is required. Early reporting is of benefit in that preparation for HIPEC will be facilitated.Standard HIPEC for positive same day cytology: If the same day cytology is positive a standardized HIPEC regimen is performed. The HIPEC methodology may be open or closed at the discretion of the surgical oncology team. The chemotherapy agents to be used are selected by the peritoneal surface malignancy team. The HIPEC treatment is maintained for 90 min at 42°C in the whole abdomen and pelvis.Review of slides obtained by same day cytology: All slides will be stored for consultation within a group meeting of pathologists/cytologists from all participating institutions. A record of positive cytologies by digital photography is recommended. All negative slides will be reviewed to assess the quality of the staining technology.Accrual: The plan is to continue the study until 20 positive same day cytology reports with HIPEC administered have been achieved. The total number of patients in the feasibility trial cannot be estimated at this time.Future plans: A randomized trial to test the efficacy of HIPEC in patients with positive same day cytology is planned.Ethics approval and consent to participate from patients for this study will be obtained.

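### Success is judged at specimen removal, which the surgical team times, so a report the operation waited for counts as on time; the 3 h requirement limits this but does not remove it

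*Protocol article*

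**What the plan says.** Under Methods, the item on time allowed for the final report states the primary goal: "The primary goal of this pilot study is to demonstrate the feasibility and reproducibility of the same day cytology". It then gives the success rule: "To be successful the results of the cytology must be available when the cancer specimen is removed". The next sentence adds "A 3 h time allowed for the final report of the same day cytology is required", without saying when the 3 h begins or whether a case must meet both conditions.

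The timing is stated differently elsewhere. The Abstract (Materials and methods) ties it to the end of the resection: "The result of this test is to be available at or before the completion of the cancer resection". Goals of this protocol says that "the results of the peritoneal cytology can be made available with 3–4 h".

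Three other statements bear on the point. Collection comes early in the operation: "The same day cytology specimen is to be collected just after access to the abdomen and pelvis has been obtained". The background section on delay in giving HIPEC (hyperthermic intraperitoneal chemotherapy) sets the aim: "An efficient and cost-effective execution of same day cytology is the goal of this protocol". Accrual is defined by a count: "The plan is to continue the study until 20 positive same day cytology reports with HIPEC administered have been achieved". The article gives no feasibility rate, denominator or threshold.

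**The concern.** Specimen removal and completion of resection are both timed by the surgical team. That team knows a report is pending, and its service is one of those whose coordination the study is meant to demonstrate. If the operation is slowed, reordered or paused until the report arrives, the case meets the rule. The rule does not separate that case from one in which the report was ready unaided. The effect has one direction: waiting can turn a failure into a success under the removal rule, never the reverse.

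The article gives some reason to take this seriously. Its own 3–4 h range includes reports later than its 3 h limit. It argues that HIPEC must follow the resection promptly, and accrual ends only when 20 positive reports have led to HIPEC.

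A favourable result could therefore conceal added operating time, which runs against the stated aim of efficiency. It would also be a poor guide to planning the later randomised trial.

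**Working it through.** **No figure to reproduce.** The article derives no on-time rate, power or total sample size. The numbers below are an illustration of size only.

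**Inputs from the article.** Success is judged at specimen removal; 3 h (180 min) is required for the report; 3–4 h is stated elsewhere (middle of the range 210 min).

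**Assumptions, not from the article.** R is the time from collection to report, normal with SD 30 min. S is the time from collection to the point at which the specimen would be removed without waiting, normal with SD 60 min. R and S are independent. The 3 h runs from collection. Whenever the report is late, the team waits up to w minutes for it.

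**Step 1, removal rule alone.** P(R ≤ S + w) = Φ((mean S + w − mean R)/√(60² + 30²)), where √4500 = 67.08. For means 180/180 and w = 60: Φ(60/67.08) = Φ(0.894) = 81%.

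**Step 2, removal rule and 3 h limit together.** P(R ≤ S + w and R ≤ 180), the integral over r up to 180 of the density of R at r times Φ((mean S + w − r)/60). Hand check for 180/180 and w = 0: the correlation of R with R − S is 30/67.08 = 0.447, so the probability is 1/4 + arcsin(0.447)/(2π) = 0.250 + 0.074 = 32.4%.

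**Results** for waits of up to 0, 30 and 60 min:

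| Mean report / removal (min) | Removal rule alone | Gain at 60 min | Both rules | Gain at 60 min | Ceiling P(R ≤ 180) |
|---|---|---|---|---|---|
| 180 / 180 | 50%, 67%, 81% | 31 points | 32%, 40%, 46% | 13 points | 50% |
| 210 / 180 | 33%, 50%, 67% | 35 points | 10%, 12%, 14% | 5 points | 16% |
| 180 / 240 | 81%, 91%, 96% | 15 points | 45.5%, 48.3%, 49.5% | 4 points | 50% |
| 150 / 150 | 50%, 67%, 81% | 31 points | 46%, 61%, 72% | 26 points | 84% |

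The range depends on the assumed means. With report 150 and removal 240, where reports seldom come after removal, a 60 min wait adds 8 points under the removal rule alone (91% to 99%) and 5 points under both rules (79% to 84%).

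**Step 3, what the 3 h limit cannot see.** Suppose a specimen could have been removed at 2 h 10 min but was held until a report at 2 h 50 min. The case passes both rules after a 40 min hold. The 3 h limit tests laboratory turnaround. Only the removal rule tests whether the result arrived in time for the operation, and that is the rule that can be influenced.

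**The case against.** The strongest objection is the 3 h sentence. A reader might infer from the removal rule alone that any late report can be made on time by waiting. If the 3 h limit is enforced from collection, that is false: a report later than 3 h fails whatever the surgical team does, and the gains shrink as the table shows. This stands as a limit on the size of the problem. It does not dispose of it, because the limit has no stated start, is not tied to the success sentence, sits beside 3–4 h elsewhere, and does not register waiting within 3 h.

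A reader might also infer that the feasibility rate is biased upward. The article does not support that. It defines no rate, and it nowhere says that an operation may be held for the report. Its text leans the other way: preparations are meant to avoid delay, HIPEC is to be available at short notice, and the background argues that delay harms the treatment. The SDs and waits used above are assumptions, and waiting the full allowance in every late case is the most that such an allowance could do. Nor does it help to call the team unblinded, since the surgeon must receive the result in order to use it.

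The removal anchor also has a purpose: it asks whether the result arrives in time to decide on HIPEC in the same operation. That is a reason to keep it, but not to count waited-for reports as in time. Case-form detail can be left to a full protocol. The success rule itself is stated in the article.

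**Conclusion.** The concern holds in a limited form. The success rule rests on an event the surgical team times, so apparent success can be raised by waiting, and the adjacent 3 h requirement is not specified well enough to be a dependable second criterion. Whether any inflation would occur cannot be told from the article.

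On the assumed distributions, a wait of up to 60 min adds about 15 to 35 points if the removal rule stands alone (means 180/180, 210/180 and 180/240). With 3 h from collection enforced as well, it adds about 4 to 13 points in those scenarios, and about 26 points if reports and removals both average 150 min. These figures depend on the assumed means, SDs, independence and full use of the waiting allowance. The direction under the removal rule does not. The measure should be tightened before the study starts, because the repair is cheap and unrecorded waiting could not be recovered reliably afterwards.

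**What to change.** 1. Reconcile the timing statements in the Abstract, Goals of this protocol and Methods: one event (specimen removal or completion of resection) and one time limit (3 h or 3–4 h). Which limit applies is for the sponsor to settle.
2. Define success by two conditions that must both be met: a clock with a recorded start and end (for example, specimen hand-off to final report) within the agreed limit, and the result being available at specimen removal.
3. Add one counting rule, for example: *A case in which specimen removal or any later step was held or reordered for the cytology report is counted as not on time.*
4. Record report time, removal time and minutes held, and report them beside the on-time result for all enrolled patients, positive and negative.

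This changes only how cases are counted, not how the operation is conducted. The cost is a few sentences and a few case-form fields taken largely from operating-room times. The on-time result may look less favourable.
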